### Recruitment {15}

The recruitment window for the study will be 36 months from the point the trial opens. Women are initially identified in the antenatal care setting of St Mary’s Hospital MFT, St Mary’s Hospital Wythenshawe and North Manchester General Hospital. Eligible participants are provided with information on the study and given sufficient time to consider participation. Those interested in the study are invited to attend an enrolment and consent visit at St Mary’s Hospital MFT. Eligible participants are invited to take part in MIMICH II. Strategies to ensure recruitment targets are met include offering incentives such as continuity of care from the trial team throughout pregnancy, 4D ultrasound scans and gift vouchers. Additionally, participants of MIMICH II will receive MIMICH branded baby grows, have their travel expenses covered and will receive postnatal care from the same trial team who performed their antenatal visits.

## Assignment of interventions: allocation

Participants will be randomised via the online gateway ‘randomisation system’ hosted by the independent provider Sealed Envelope.

### MIMICH sequence generation {16a}

The sequence will be computer generated within the Sealed Envelope platform. Participants will be randomised (1:1) using minimisation with a random element controlling for:Type of diabetes (diagnosed < 24 weeks’ gestation, diagnosed > 24 weeks’ gestation)Risk factor for placental disease (uteroplacental or maternal risk factor)Gestational age (6 + 0 to 11 + 6 weeks, 12 + 0 to 23 + 6 weeks, 24 + 0 to 30 + 0 weeks)

The sequence will be computer generated. Participants will be randomised (1:1) using minimisation with a random element controlling for:Type of diabetes (diagnosed < 24 weeks’ gestation, diagnosed > 24 weeks’ gestation)Risk factor for placental disease (uteroplacental or maternal risk factor)Gestational age (6 + 0 to 11 + 6 weeks, 12 + 0 to 23 + 6 weeks, 24 + 0 to 30 + 0 weeks)

For each new participant, the algorithm calculates the imbalance that would result from assigning them to each treatment arm. The arm that minimises imbalance is selected with high probability (default 80%). With the remaining probability (20%), allocation is made to the alternative arm. If both arms would produce equal balance, allocation is determined with equal probability (50:50).

This approach maintains a close balance between groups across important prognostic factors, whilst the random element preserves allocation unpredictability. The randomisation sequence is generated and maintained centrally within the Sealed Envelope system, ensuring full allocation concealment from investigators and participants until the point of assignment.

### Concealment mechanism {16b}

The randomisation process is centrally and independently managed by Sealed Envelope, which ensures concealment of the allocation sequence until the time of intervention allocation.

### Implementation {16c}

The responsibility for enrolling participants into the trial lies with appropriately trained healthcare professionals at the site, who will have to confirm the eligibility criteria before they enter the minimisation factors into the online randomisation system (sealed envelope) to randomise participants. Using minimisation with a random element, the system will allocate the treatment, and users will be notified of the assigned treatment allocation for the participant. Allocation concealment will be ensured, as the service will not release the randomisation code until the patient has been recruited into the trial, which takes place after all baseline measurements have been completed.

### Blinding {17a and 17b}

To ensure women are effectively and safely treated during the trial with a focus on normalising blood glucose levels, participants, clinicians or members of the trial management team are not blinded to participant allocation and therefore no unblinding procedures are required. Data analysts (analysis of 3D thigh volumes) are blinded to treatment allocation.

### Data collection and management {18a}

Plans for assessment and collection of trial outcomes are presented in the Outcomes section above. Before commencing recruitment, all trial team members receive training on the study designs, protocol procedures (within the Site Initiation Visit) and data collection procedures (REDCap database training). All members of the site research team are expected to work in accordance with the GCP guideline and are required to provide proof of their GCP training and relevant experience.

Baseline information such as demographic data and pre-pregnancy health information, study visit data and outcome data are captured during study visits and from health records notes where clinical data is routinely collected during the antenatal period, at birth and up to hospital discharge.

Research specific data such as skinfold thickness information, treatment adherence in the seven days prior to the visit, current medications and baby measurements at birth and postnatally will be captured though study-specific source data collection forms and recorded contemporaneously during each study visit.

Instruments for data collection related to the trial include ultrasound machines, biochemical assays and glucose monitoring, and these are summarised in Appendix A.

Participant satisfaction and acceptability of trial intervention is captured in an unvalidated trial-specific questionnaire (Appendix B).

For participants who are ineligible for post-trial follow-up, outcomes are captured up to primary hospital discharge for each of the women or baby post-birth, and 28 days post-birth for neonates. For those who continue in the MIMICH II study, outcomes are collected up to 12–48 months postnatally for both the mother and baby. The case report forms for both MIMICH and MIMICH II have been created within the REDCap database hosted by the University of Manchester. PDFs of all study instruments have been downloaded and filed in the investigator site file (ISF) and trial master files (TMF).

Data monitoring procedures include the use of range control within data entry fields, gestational age calculations embedded in date fields and verification of all entered data by an independent data monitor; all data is verified against case report forms and case note review, with queries actioned and logged using REDCap functionality.

### Plans to promote participant retention and complete follow-up {18b}

All recruits will receive continuity of care in the specialist research clinic to encourage participation and retention. Confirmation of a willingness to continue in the trial will be confirmed at each clinical/study visit. Participants who choose to end their participation in the MIMICH trial but consent to the collection of birth and outcome data will be classed as discontinuations. In this case, no further data during antenatal care will be collected, but maternal, neonatal and birth details will be collected. Participants who end their participation and decline collection of their birth and outcome data will be classed as withdrawals. In this case, all data collection from the point of withdrawal will cease. Participants who discontinue or withdraw from MIMICH will not be eligible for MIMICH II. Participants who deviate from their allocated treatment arm will continue in the study, with treatment exposure recorded at each visit.

### Data management {19}

Trial data are collected and stored according to GCP guidelines. Processes to facilitate the accuracy of the trial data are detailed in the data management plan. Coding and validation are agreed upon between the trial manager and statistician, and the study database is signed off once the implementation of these has been assured. Only minimal identifiers (e.g. initials, date of birth, last four digits of NHS numbers and postcodes) will be included in the trial database. All paper records will be kept in locked filing cabinets, in a secure office during the trial. Access to partially anonymised trial data is controlled by the CI, with access approved by the REDCap data administrator. Electronic and hard copy data will be retained in line with the University of Manchester’s archiving standard operating practice (SOP).

### Confidentiality {27}

Personal information recorded is regarded as strictly confidential and handled and stored following the Data Protection Act 2018 (and subsequent amendments). Women are always identified using their unique study number. No information by which a woman may be identified is disclosed to any third party other than those directly involved in the treatment of the participant.

### Plans for collection, laboratory evaluation and storage of biological specimens for genetic or molecular analysis in this trial/future use {33}

Blood samples will be collected with permission from participants at every study visit. Where possible, placentas will be collected after birth. Samples will be stored in the Maternal and Fetal Health research laboratory for the duration of the trial, after which time they will be transferred to the Tommy’s National Biobank if consented to by the participants. Samples will be destroyed after the trial has ended if biobank storage is declined.

## Statistical methods

### Statistical methods for primary and secondary outcomes {20a}

The statistical analysis will be conducted according to the approved statistical analysis plan. Baseline characteristics of the trial population will be presented as mean and standard deviation (or median and interquartile range as appropriate). The main analysis will be an intention to treat analysis for the primary and secondary outcomes. For the primary outcome, the average z-score for estimated foetal weight (calculated using the modified EFW formula which incorporates TVol [44]) performed between 20 and 29 weeks will be calculated. This will be 1–3 scans per woman. The delta between the birthweight z-score and the 20–29-week z-score will be calculated. Delta z-scores will be compared between treatment groups using linear regression models adjusted for baseline z-score and minimisation variables (these will be confirmed in the final statistical analysis plan). All secondary outcomes will be reported as described in the outcomes section and analysed in accordance with the prespecified statistical analysis plan.

Missing data for baseline prognostic factors are not anticipated since they must be recorded to allocate treatment. All observed outcome data will be included in the analyses. As this is an exploratory study, we will focus on reporting the amount of missing data. We will report the number (%) of participants withdrawing fully from the trial and lost to follow-up by treatment arm. Reasons for missingness may be important, and these will be tabulated by treatment arm and documented as far as possible. Main analyses will be performed using STATA (StataCorp, College Station, TX, USA).

### Interim analyses {21b}

No interim analyses are planned for the trial.

### Methods for additional analyses (e.g. subgroup analyses) {20b}

Planned subgroup analyses on the primary outcome will investigate interactions between treatment effects and minimisation factors, with separate estimates and CIs reported for these subgroups of participants. In order to explore potential mechanism of action, exploratory analyses will estimate the effect of treatment received on the foetal growth outcomes.

### Methods in analysis to handle protocol non-adherence and any statistical methods to handle missing data {20c}

Every effort will be made to reduce missing data through prospective data monitoring. Level of missing data will be reported for all primary and secondary outcomes.

### Plans to give access to the full protocol, participant-level data and statistical code {31c}

Anonymised data and all statistical code will be made available on request to the chief investigator.

## Oversight and monitoring

### Composition of the coordinating centre and trial steering committee {5d}

The trial is coordinated by the Maternal and Fetal Health Research Centre. All aspects of the conduct and progress of the trial and the day-to-day running of the trial are monitored by the Trial Management Group (TMG). The TMG meets monthly and includes the chief investigator, project manager and trial research midwives. The TMG reports to the Trial Oversight Committee (TOC). The TOC meets at least annually, and as required depending on the needs of the trial, and is responsible for providing overall oversight of the trial, including practical aspects of the trial and ensuring the trial is run safely for the participants. TOC members include an independent chair, two other independent members, a PPI representative, the trial statisticians, the project manager and the CI. The TOC has responsibility for overseeing the conduct of the trial and reviewing the recruitment rate, the baseline characteristics of the trial participants and rates of adverse outcomes. TOC reports are presented to the TOC per arm but not labelled by allocation.

### Adverse event reporting and harms {22}

Adverse events are collected for MIMICH study participants and their babies, from consent (from birth for babies) up to primary discharge after birth. AEs are commonly encountered in this population of pregnant women as a part of the clinical condition of pregnancy and diabetes in pregnancy. As the safety profile of metformin is well-characterised, a strategy of targeted reporting of AEs is used without affecting the safety of participants. Adverse events are separated into expected AEs, which are recorded on the case note review but not reported, and those that are reportable.

The following are considered expected in this population of pregnant women or a result of the usual clinical care and, as such, will be recorded in the participant’s medical record (including where a woman offers information to a research team) but not reported as (S)AEs:

#### Maternal events

Intolerance to metformin (usual care arm)Episodes of hypoglycaemia (not requiring hospitalisation)Admission in active labourAdmission for cervical ripening or induction of labourAdmission for caesarean sectionAdmission for assessment for suspected foetal compromise, including poor growth, or reduced foetal movementsAdmission for the treatment of infection/sepsisAdmission for monitoring for diabetes, hypertension or pre-eclampsia, antepartum haemorrhage, suspected preterm labour, pre-labour rupture of the membranes or other reasons for monitoringAdmission for psychiatric or social reasonsAdmission for unstable lie or external cephalic versionAdmission for postpartum complicationsKnown complications of pregnancy that are collected for every woman as part of outcome collection (including, but not limited to, pre-eclampsia, postpartum haemorrhage, postpartum haemorrhage requiring transfusion or hysterectomy)Any adverse event that is expected during pregnancy including but not limited to tiredness, constipation and back pain. Maternal undesirable effects of the allocated medication regime will be recorded at each trial visit

#### Foetal and neonatal events

Known foetal and neonatal complications of pregnancy that are collected for every infant as part of outcome collection, including, but not limited to:Neonatal unit admissionMiscarriagePreterm delivery (< 37 completed weeks’ gestation)Neonatal complications (including but not limited to hypoglycaemia, seizures, encephalopathy, need for respiratory support, sepsis, intraventricular haemorrhage, confirmed infection, necrotising enterocolitis, retinopathy of prematurity, congenital anomaly, intraventricular haemorrhage)

For the purposes of this trial and its follow-up (MIMICH II), congenital abnormalities will be considered AEs but not SAEs. As the trial treatment for MIMICH is already licensed and given as or part of standard treatment in this patient population, it is not considered likely that either treatment arm will cause or contribute to a congenital anomaly over and above the risk associated with maternal diabetes.

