Neonatal outcomes—clinical birth outcomes obtained from case note review:Foetal loss (prior to 24 weeks’ gestation and from 24 + 0 weeks’ gestation (stillbirth))Known early neonatal death (up to 7 days from birth)Known late neonatal death (between 7 and up to 28 days from birth)Gestational age at birthBirthweight, birthweight centile, birthweight z-scoreNeonatal unit admission (separation of baby from mother), principal recorded indication for neonatal unit admission and length of stay in neonatal unit (and level of care)Apgar score (5 min)Umbilical arterial pH at birthNeed for respiratory support and type of respiratory support neededLowest blood glucose measurement and need for treatment for neonatal hypoglycaemiaNeonatal seizures, intracranial haemorrhage, necrotising enterocolitisBreastfeeding at discharge

Exploratory outcomes—additional research outcomes:Longitudinal changes in angiogenic markers (sFlt, PlGF)—measured in research blood samples (batch analysis end of study)Maternal skinfold measurements (delta change from baseline visit adjusted for gestation)HOMA-IR (measured at 30–34 weeks ± 2 weeks)—measured in research blood samples (real time in the biochemistry lab)Ponderal index (foetal weight in grams × 100/(foetal length in centimetres)Neonatal measurements within 72 h of birth (crown-heel lengths, weight, head/abdominal circumferences, biceps, triceps, subscapular skinfold thicknesses)Erythropoietin (marker of intrauterine stress) [45, 46]

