#### Adverse events

Adverse event recorded (number of women and number of adverse events) during treatment only. All AEs and SAEs identified will be recorded in the trial database and will be reviewed and signed by the PI. The trial sponsor will also be made aware of any SAEs that occur on trial and will be sent copies of the completed SAE forms.

As postnatal follow-up visits will not require treatment to be taken, any adverse events occurring during this time will not be recorded in the trial database.

If any abnormality is found in the bloods, blood pressure or echocardiograms at any point during active treatment or postnatal follow-up, this will be explained to the participant and we will inform their GP or refer to the appropriate clinical team depending on the clinical significance of the finding.

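### Five neonatal harms, congenital anomaly among them, are exempted from (S)AE reporting as collected outcomes but are not in the outcome list, so their reporting by arm is not assured

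*Protocol article*

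**What the plan says.** Adverse event reporting and harms {22} describes a targeted strategy: "Adverse events are separated into expected AEs, which are recorded on the case note review but not reported, and those that are reportable". The events then listed as expected go into the participant's medical record "but not reported as (S)AEs".

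Under Foetal and neonatal events, the exempt class is described as "Known foetal and neonatal complications of pregnancy that are collected for every infant as part of outcome collection, including, but not limited to". It names neonatal unit admission, miscarriage, preterm delivery and a bracketed set of neonatal complications. That set starts with hypoglycaemia and seizures and goes on: "encephalopathy, need for respiratory support, sepsis, intraventricular haemorrhage, confirmed infection, necrotising enterocolitis, retinopathy of prematurity, congenital anomaly, intraventricular haemorrhage". The following paragraph says that "congenital abnormalities will be considered AEs but not SAEs" and adds that neither arm is thought likely to contribute to an anomaly beyond the risk from maternal diabetes.

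The Adverse events section under Outcomes {12} has two further statements: "Adverse event recorded (number of women and number of adverse events) during treatment only" and "All AEs and SAEs identified will be recorded in the trial database and will be reviewed and signed by the PI".

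The neonatal outcomes themselves are set out under Outcomes {12}, MIMICH, as birth outcomes taken from case note review.

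**The concern.** Exempting an event from (S)AE reporting because it is already captured as an outcome is sound, provided that the outcome list contains the event. Where it does not, the event has left one reporting route without a stated place in the other.

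Congenital anomaly is the item where this matters most. Randomisation is open from 6+0 weeks, and minimisation has a level for 6+0 to 11+6 weeks, so some participants will be allocated early in pregnancy. The protocol handles anomalies on an assumption that neither arm adds to the risk. A descriptive count by arm would let readers set the trial's own data beside that assumption. For sepsis, infection, encephalopathy and retinopathy of prematurity, the question is whether the harms report of a trial about pregnancy treatment will show all the neonatal morbidity that the protocol says it collects.

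**Working it through.** No figure in the protocol is at issue. The check sets the exempted events beside the neonatal outcome list.

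**Step 1. Count the exempted items.** Three are named singly (neonatal unit admission, miscarriage, preterm delivery). The bracket names 11 complications, with intraventricular haemorrhage appearing twice, so 11 − 1 = 10 are distinct. Total: 3 + 10 = 13.

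**Step 2. Match each to the neonatal outcomes.**

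| Exempted event | Entry in the neonatal outcome list | Match |
|---|---|---|
| Neonatal unit admission | Same | Direct |
| Miscarriage | Foetal loss before 24 weeks | Direct |
| Preterm delivery | Gestational age at birth | Derivable |
| Hypoglycaemia | Lowest glucose and need for treatment | Direct |
| Seizures | Same | Direct |
| Respiratory support | Need and type | Direct |
| Intraventricular haemorrhage | Intracranial haemorrhage | Covered by the broader term |
| Necrotising enterocolitis | Same | Direct |
| Encephalopathy | None | No |
| Sepsis | None | No |
| Confirmed infection | None | No |
| Retinopathy of prematurity | None | No |
| Congenital anomaly | None | No |

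Eight match and 13 − 8 = 5 do not. The exempt list is open-ended and the outcome list is not, so five is the count among named events only.

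**Step 3. Compare the statements on how adverse events are handled.**

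- *Status of congenital anomaly.* It is in the list exempt from (S)AE reporting. The next paragraph calls it an AE but not an SAE. Staff are not told whether an AE entry is required.
- *Where events are recorded.* The Adverse events section says the trial database, for all identified AEs. Section {22} says the case note review, and then the participant's medical record, for expected events.
- *Who is counted.* The Adverse events section names women and events, during treatment. Section {22} collects events for babies from birth to primary discharge. No count of infants is named.

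**Step 4. Look for the same mismatch among maternal events.** The Maternal events list exempts known complications on the ground that they are collected for every woman. Its examples include postpartum haemorrhage requiring transfusion or hysterectomy. The maternal outcomes list postpartum haemorrhage only as blood loss above 1000 mL. The haemorrhage is counted, but the more severe form is not separately listed.

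**The case against.** The strongest reply is that this is an article. The full protocol, the case report form and the analysis plan are not shown and may hold fields for all five events. The exemption text itself asserts that the events are collected. That stands as far as collection goes, and no data need be presumed lost. It does not remove the mismatch, because the article gives both the reason for the exemption and the list that should bear it out, and they disagree on five items.

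A second reply is that the scheme in section {22} treats exempt events as a kind of AE, so an anomaly can be at once an AE, not an SAE, and expected. It can be read that way. The wording still leaves open whether an AE entry is made, and the rule that all identified AEs enter the database points the other way from recording only on the case note review.

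A third reply is that section {22} also exempts events as expected in this population or as results of usual care, so collection as outcomes is not the only ground. That is true, but it is how the protocol describes the neonatal class, and it is the part that would secure a report by arm.

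A reader might go further and infer that these harms would have no report by arm at all. The documents do not support that:

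- All identified AEs are to enter the trial database.
- The oversight committee reviews adverse outcome rates in reports separated by unlabelled arm (section {5d}).
- Some of these events would surface through the "principal recorded indication for neonatal unit admission".

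A reader might also infer the same gap for antenatal admissions. That does not follow. Those admissions are exempted as expected events, not as collected outcomes. Admissions for labour, induction and caesarean section correspond to the listed onset and mode of birth outcomes. Glycaemic control and crossover are measured directly.

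**Conclusion.** The point holds as a mismatch between stated rules. Five of 13 named neonatal events are exempted as collected outcomes without being listed as outcomes, and the status of congenital anomaly is stated in two ways. Reporting of these five harms by arm is not assured. The maternal parallel, on transfusion or hysterectomy for haemorrhage, is smaller.

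The size is best given as this count of items. The number of affected infants cannot be estimated from the documents. No anomaly rate is given, foetal abnormality known before consent is an exclusion, and entry runs to 30+0 weeks, so a general rate applied to all infants would not fit this population.

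The conclusion assumes that the neonatal outcome list in the article is the operative one. If the full protocol or analysis plan already lists the five events by arm, what remains is to align the wording.

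**What to change.** 1. Add congenital anomaly, sepsis, confirmed infection, encephalopathy and retinopathy of prematurity to the neonatal outcomes as descriptive counts of infants by arm, without tests. Alternatively, limit the neonatal exemption to events that are in the outcome list, so that the others are recorded and summarised as AEs by arm.
2. Reconcile the neonatal outcomes, the Adverse events section, section {22} and Foetal and neonatal events. They should say whether congenital anomaly is a recorded AE or an exempt event, where exempt events are recorded, and that infants as well as women are counted.
3. Treat haemorrhage requiring transfusion or hysterectomy in the same way: list it, or take it out of the group exempted as collected outcomes.

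The cost is small. The events are said to be on the case note review already, so the change is to wording and to a few descriptive tables. The downside is that those tables will hold small counts. They should be read as description, and a further split of anomalies by gestation at entry is not needed.
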